To this end, the purpose of the present study is to investigate the short- and long-term effectiveness of cTBS over the right cerebellum in augmenting language recovery in chronic post-stroke aphasia in a randomized, sham-controlled design. In addition to aphasia test batteries and speech acoustic analyses for evaluation of treatment outcome, the resting-state functional magnetic resonance (RS-fMRI) is also used to explore the neural mechanisms underlying aphasia rehabilitation. The previous studies have shown associations between improved spelling or phonemic fluency and increased resting-state functional connectivity between the cerebellum and language-related cortical regions for patients with chronic post-stroke aphasia or healthy individuals following tDCS over the right cerebellum (Sebastian et al., 2016; Turkeltaub et al., 2016). Accordingly, we hypothesize that, following cTBS over the right cerebellum, patients with chronic post-stroke aphasia will exhibit improved language functions and increased functional connectivity within the cerebro-cerebellar language network. This randomized, sham-controlled study provides significant new insights into the therapeutic efficacy of cTBS over the right cerebellum to augment SLT for post-stroke aphasia and the underlying neuroplastic mechanisms.

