### Sample Size

The sample size was calculated using PASS software (v.15.0) on the basis of previous studies. With an effect size of 0.5 based on the WAB-AQ (Hu et al., 2018), we expect that the target effect size had 80% of power with a type I error of 5% (α = 0.05). Thus, the sample size of each group is at least 16. With an assumption of 20% dropout rate, a sample size of 20 participants will be targeted for each group.

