### Outcome Measures

The primary outcome measure is the WAB assessment that is divided into four subitems including spontaneous speech, auditory verbal comprehension, repetition, and naming. The original scores of the four items are 20, 200, 100, and 100, respectively. An aphasia quotient (AQ) is calculated using the following formula: AQ = (spontaneous speech + auditory verbal comprehension/20 + repetition/10 + naming/10) × 2. The AQ indicates the severity of aphasia and can be used as an index for evaluating the improvement and deterioration of aphasia. The highest AQ score is 100, and the normal range is 98.4–99.6. AQ <93.8 is considered as aphasia.

In addition to the WAB scores, there are several secondary measures of treatment outcome including BDAE, Boston Naming Test (BNT), speech acoustic parameters, and RS-fMRI. BDAE is used to measure the severity of impaired language function that can be divided into five grades from severe to mild. The BNT is an assessment tool to measure the confrontational word naming of 30 object pictures. The speech acoustic parameters include fundamental frequency, intensity, speaking rate, maximum phonation time, range of voice features, and speech intelligibility. Speech signals are recorded using a laptop at sampling frequency 44.1 K Hz and Praat software is used to extract acoustic parameters.

RS-fMRI data are acquired using a 3.0 T MAGNETOM Skyra scanner (Siemens, Germany). The participants are instructed to lie still with their eyes closed and think of nothing. Functional images are obtained using echo-planar imaging (EPI) pulse sequence with the following parameters: repetition time (TR) = 2,000 ms; echo time (TE) = 30 ms; 35 slices, field of view (FOV) = 224 mm × 224 mm; slice thickness = 3.5 mm; layer spacing 0.7 mm; flip angle (FA) = 90°; acquisition matrix 64 × 64; voxel size = 3.5 mm × 3.5 mm × 3.5 mm. For registration purposes, a set of high-resolution structural images are acquired through a T1-weighted sequence: 192 sagittal slices; slice thickness = 1 mm; TR = 6.6 ms; TE = 3.1 ms; FA = 12°; FOV = 256 mm × 256 mm. The scanning lasted for 8 min and produced 240 brain volumes.

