After the preprocessing, regional homogeneity (ReHo), degree centrality (DC), and seed-to-voxel analyses are conducted to measure the local and global functional connectivity within the language networks. ReHo is calculated based on the Kendall’s coefficient of concordance (KCC), which measures the consistency of the time signal between a voxel and surrounding voxels. Higher ReHo values represent better consistency between the local voxel and the regional brain activities. DC values reflect the network connection intensity between a certain voxel and all of the brain, indicating the importance of this voxel as the network node (Zang et al., 2004). One-way ANOVAs are conducted on the ReHo and DC values to explore differences across the conditions within the predefined gray matter mask. The ANOVA F maps are corrected using Gaussian random field (GRF) correction (single voxel *p* < 0.001, cluster level *p* < 0.05). The ReHo and DC values of the peak voxels in the surviving clusters are extracted and entered into SPSS (v. 22) for further analysis. Seed-to-voxel analyses are conducted with *a priori* regions of interest (ROI). The ROIs consist of language-related regions in cerebellar Crus I; IFG pars opercularis; IFG pars triangularis; primary motor cortex (M1); anterior and posterior STG; angular gyrus; anterior and posterior supramarginal gyrus (SMG), which are selected from the AAL atlas (Tzourio-Mazoyer et al., 2002). These ROI-based functional connectivity maps are statistically compared between pre- and post-treatment and between real cTBS and sham stimulation group. Differences across the conditions are considered significant when *p* < 0.05 at the voxel level, with a false discovery rate (FDR) cluster corrected *p* < 0.05.

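### ReHo and DC values taken at ANOVA-selected peak voxels cannot support a further p-value or effect size for the condition differences that selected them, and the plan does not rule this out

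*Protocol article*

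**What the plan says.** All of this stands in the RS-fMRI part of Data Analysis in the protocol article, unless another section is named.

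- **Selection test:** "One-way ANOVAs are conducted on the ReHo and DC values to explore differences across the conditions within the predefined gray matter mask".
- **Threshold:** the F maps are GRF-corrected at "single voxel *p* < 0.001, cluster level *p* < 0.05".
- **Values taken forward:** "The ReHo and DC values of the peak voxels in the surviving clusters are extracted and entered into SPSS (v. 22) for further analysis". The text does not say whether this means pairwise comparisons, effect sizes or correlation with language scores.
- **Contrast within the same section:** "Seed-to-voxel analyses are conducted with *a priori* regions of interest (ROI"). These regions come from an atlas, so the results do not select them. The comparison of pre with post and of real with sham is spelled out only for these seed maps.
- **Role of imaging:** Outcome Measures says "there are several secondary measures of treatment outcome including BDAE, Boston Naming Test (BNT), speech acoustic parameters, and RS-fMRI". The Introduction says that RS-fMRI "is also used to explore the neural mechanisms underlying aphasia rehabilitation".
- **Numbers:** "Thus, the sample size of each group is at least 16" (Sample Size), with 20 per group targeted to allow for 20% dropout.

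**The concern.** A peak voxel is carried forward because it shows the largest F in its cluster, in these same patients. If the same condition difference is then tested or estimated at that voxel, the data are used twice. GRF correction protects the claim that a cluster exists. It does not protect a later estimate or test at the peak.

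The step matters because the first stage is an omnibus F. It can say that some condition differs, but not that real differs from sham. Both arms receive speech-language therapy (Interventions), so a cluster could survive because of a change common to both arms. The only ReHo/DC follow-up that the article states is the one on the selected peaks. A real-versus-sham statement about ReHo or DC would therefore have to come from that step, and could be read as a neural effect of cTBS that the data do not establish.

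**Working it through.** The plan gives no figure of its own for this step, so there is none to reproduce. The checks below size the selection effect.

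**Inputs from the article:** voxel threshold p<0.001; 16 or 20 per group; two groups; two imaging time points (before and after the intervention).

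**Assumptions of this check:** true d of 0 or 0.5; voxels independent where several are searched; cluster extent and spatial smoothing not modelled.

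**1. Two-arm contrast, one voxel.** The smallest |d| that can be selected is t(0.9995; 2n−2) × √(2/n).

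- n = 20: 3.566 × √(2/20) = 1.13
- n = 16: 3.646 × √(2/16) = 1.29

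Mean observed |d| given selection, by simulation:

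| n per group | true d = 0 | true d = 0.5 |
|---|---|---|
| 16 | 1.41 | 1.46 |
| 20 | 1.23 | 1.28 |

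A true 0.5 is thus overstated by 1.28/0.5 = 2.6 times (n = 20) or 1.46/0.5 = 2.9 times (n = 16). If the peak of 500 independent voxels is taken, all with true d = 0.5, the means rise to 1.62 (n = 20) and 1.79 (n = 16).

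**2. Four-cell one-way ANOVA (2 groups × 2 phases, cells treated as independent).** In SD units, the squared deviations of the four cell means sum to 3F/n. For a given range R, that sum is largest when two means lie at each end, and it is then 4 × (R/2)² = R². Hence R is at least √(3F/n).

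- n = 20: critical F(3,76) = 6.00; R ≥ √(3 × 6.00/20) = 0.95 SD; t ≥ 0.949/√(2/20) = 3.00; p ≤ 0.0036; Bonferroni over 6 pairs ≤ 0.022.
- n = 16: critical F(3,60) = 6.17; R ≥ 1.08 SD; t ≥ 3.04; p ≤ 0.0035; Bonferroni ≤ 0.021.

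So at least one adjusted pairwise comparison, using the ANOVA error term, is below 0.05 once the voxel is selected.

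**3. Could the follow-up wrongly point to treatment?** Simulation with 20 per group, one voxel and no treatment effect. The entries are rejection rates among selected voxels for tests at nominal 5%, with a pre/post correlation of 0 or 0.5.

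| Truth | Post-treatment real vs sham | Group-by-phase interaction |
|---|---|---|
| Common phase change of 0.5 SD | 16% (corr. 0), about 38% (corr. 0.5) | 17%, 12% |
| No effect at all | 57%, 91% | about 55%, 13% |

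The last row describes false-positive voxels only. The GRF correction is there to make such clusters rare.

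**4. Correlation with an unrelated language change (20 per group, peak of 500 voxels).** Within group, the type I error is 4.6% to 5.2%. Pooled over both groups it is 4.8% if language change does not differ by group, 13% to 17% if it differs by 0.5 SD, and 46% if by 1.0 SD.

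**The case against.** The strongest reply is that the article never says the selecting contrast will be re-tested. The SPSS step is unspecified, and a condensed article may leave its content to a fuller document. Legitimate uses exist: reading off the direction of an effect that the GRF-corrected map has already established, or correlating values with language change within group. A reader might infer that the planned ReHo and DC results are circular and inflated as such, or that every use of the extracted values is tainted. The documents support neither inference. The bias arises only if a p-value or effect size is attached to the selecting differences, or if a correlation is pooled over arms that differ in language change.

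It is also fair that the magnitude is a simplified case. The factor in the one-way ANOVA is not defined, the data are smoothed, and a cluster threshold applies. The stakes are limited too: RS-fMRI is a secondary measure used to explore mechanism, and no efficacy conclusion rests on these values. Finally, whole-region means can miss focal effects, and patients have left-hemisphere strokes (Participants) of varying site and size (Discussion), so left-hemisphere regions may include lesioned tissue.

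All of this stands. It makes the point conditional but does not remove it. The article does state which voxels go forward and from which data, and that choice is unsuitable for inference on the selecting contrast, whatever a fuller plan adds.

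**Conclusion.** The point holds in conditional form. The selection rule and the reuse of the same patients are stated; the inferential use is not, though the text leaves it open. If the peak values are used to test or estimate the differences that selected them, the result is non-independent and biased upward. The algebraic bounds (|d| at least 1.13 or 1.29; a largest pairwise difference of at least 0.95 SD with 20 per cell) follow from the stated voxel threshold and group sizes, given a two-arm or independent four-cell layout. The mean inflation of 2.6 to 2.9 times further assumes a true d of 0.5. These figures show the order of the problem; they do not forecast this trial's results.

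The GRF-corrected maps, the seed-to-voxel analysis, the primary WAB analysis and within-group correlations are not affected. A pooled brain-behaviour correlation can be. The change is worth making before the data are seen, because no later analysis of the same peaks removes the selection.

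**What to change.** 1. State that values from surviving clusters, preferably cluster means rather than peak voxels, serve only to describe the direction of the GRF-corrected effect, with no new p-value or effect size for the contrast that selected them.
2. Take any inferential real-versus-sham or pre-versus-post test, any effect size and any pooled correlation with language change for ReHo and DC from mean values in the a priori regions already listed in Data Analysis, led by right Crus I, the stimulated site.
3. Exclude lesioned voxels from left-hemisphere regions.
4. Say what the further analysis in SPSS consists of. Within-group correlations may keep the extracted values.

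**Cost:** no new data are needed, only a change of wording, a different extraction mask and lesion masking on the left. The real price is scientific: region means may dilute focal effects, and the reported imaging effects will look smaller.

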### Safety

Adverse effects are defined as any negative experiences that occur to the patients who underwent the cerebellar cTBS or MRI scanning. All adverse effects will be reported by the investigator during the treatment and within 1 week after the end of treatment. Particularly, seizures that are the most severe TMS-related adverse effects with a risk of approximately 0.02%, are only expected to occur during or immediately after cerebellar cTBS. In addition, adverse effects that occur during the MRI scanning will be reported within 24 h. Earplugs will be provided to patients to protect their hearing against noise. Any serious incident will be immediately reported to the Medical Research Ethics Committee of Wuxi Tongren Rehabilitation Hospital.

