**Methods:**

In this randomized, sham-controlled clinical trial, patients (*n* = 40) with chronic post-stroke aphasia received 10 sessions of real cTBS (*n* = 20) or sham cTBS (*n* = 20) over the right cerebellar Crus I+ a 30-min speech-language therapy. The Western Aphasia Battery (WAB) serves as the primary measure of the treatment outcome. The secondary outcome measures include the Boston Diagnostic Aphasia Examination, Boston Naming Test and speech acoustic parameters. Resting-state fMRI data were also obtained to examine treatment-induced changes in functional connectivity of the cerebro-cerebellar network. These outcome measures are assessed before, immediately after, and 12 weeks after cerebellar cTBS intervention.

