## Methods

### Study Design

This is a prospective, randomized, sham-controlled, single-center study (Registration number: ChiCTR210049828) that will be conducted in the Department of Neurorehabilitation, Wuxi Tongren Rehabilitation Hospital, China. Hospitalized patients with chronic post-stroke aphasia are recruited to participate in the study. They are randomly assigned with a ratio of 1:1 to a real or sham stimulation group. Details about the study design and data collection are shown in Figure 1 and Table 1. On the day of enrollment (T0), after the end of cerebellar cTBS intervention (T1), and 12 weeks post-treatment completion (T2), aphasia test batteries and speech acoustic analyses are performed to evaluate language functions in post-stroke aphasia. Also, RS-fMRI data are collected before and after the end of the intervention. This study has been approved by the Ethics Committee of Wuxi Mental Health Center and Wuxi Tongren Rehabilitation Hospital (WXMHCIRB2021LLky078).

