**FIGURE 1 F1:**
[figure not shown]
Flow chart of study procedure. cTBS, continuous theta burst stimulation.

**TABLE 1 T1:** Overview of data collection and study timings.

Study period visits	Pre-enrollment	T0	T1	T2
Relative start of treatment days	−1 week	Day 0	±3 days after intervention	±3 days after 12 weeks of intervention
Screening (in-/exclusion criteria)	×			
Written informed consent	×			
Medical history	×			
Randomization		×		
NIHSS		×		
WAB		×	×	×
BDAE		×	×	×
BNT		×	×	×
Acoustic evaluation		×	×	×
RS-fMRI		×	×	

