### Interventions

The application of cerebellar cTBS is administered using Magneuro 100 (Vishee Medical Technology Co., Ltd., Nanjing, China) equipped with a figure 8-shaped coil (7 cm out diameter). Before intervention, a single-pulse TMS will be applied over the right primary motor cortex to determine active motor threshold (AMT). The AMT is defined as the lowest stimulus intensity that produces a motor evoked potential (MEP) of >200 μV in at least 5–10 consecutive trials with 10% maximal voluntary contraction of the first dorsal interosseous muscle of the non-paretic hand (Koch et al., 2020). Each participant receives real or sham cTBS over the Crus I of the right lateral cerebellum (3 cm right and 1 cm inferior to the inion) at 80% of AMT (Lin et al., 2022). A standard cTBS protocol consists of bursts of 3 pulses at 50 Hz that are repeatedly presented at 5 Hz, resulting in a total of 600 pulses in 40 s. The coil is oriented vertically to the target with the handle pointing superiorly during real stimulation; while the stimulation face of the coil is turned 90°, so that the side of the coil is placed on the target during sham stimulation (Rastogi et al., 2017). Immediately following real or sham cerebellar cTBS, all participants receive a 30-min SLT that includes training on comprehension, expression of spoken language, semantic, and phonological processing. The content of SLT will be modified based evaluation of language function on an individual level. Totally, each participant receives 10 sessions of cerebellar cTBS coupled with SLT (5 sessions per week) within 2 weeks.

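### Adverse-effect reporting stops 1 week after treatment although outcomes run to 12 weeks, and no inquiry about events is stated for the T2 visit

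*Protocol article*

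**What the plan says.** Four parts of the protocol article bear on this.

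- **Safety, definition.** "Adverse effects are defined as any negative experiences that occur to the patients who underwent the cerebellar cTBS or MRI scanning". The definition is broad and sets no time limit of its own.
- **Safety, window.** "All adverse effects will be reported by the investigator during the treatment and within 1 week after the end of treatment". The same section says that seizures are expected only during stimulation or directly after it, and puts their risk at about 0.02%. It closes with a duty to report serious incidents to the ethics committee at once, and gives that duty no end date.
- **Outcome schedule.** The Abstract says: "These outcome measures are assessed before, immediately after, and 12 weeks after cerebellar cTBS intervention". Study Design repeats this for T2: "12 weeks post-treatment completion (T2), aphasia test batteries and speech acoustic analyses are performed to evaluate language functions in post-stroke aphasia". Table 1 lists WAB, BDAE, BNT and acoustic evaluation at T2, with a window of ±"3 days after 12 weeks of intervention".
- **Aim.** The Introduction sets out to study the "short- and long-term effectiveness of cTBS" over the right cerebellum.

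**The concern.** Benefit and harm are followed over different periods. Benefit is measured to week 12 and is meant to support a long-term statement. Adverse effects, on the protocol's own broad definition, are reported only to week 1 after treatment. The one timing reason in the Safety section concerns seizures, so it does not explain why reporting of every other negative experience also stops at week 1.

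Two things are at stake. First, a 12-week benefit would be reported beside harms collected over a much shorter period, with no stated comparison of later events between arms. Second, the T2 scores become harder to interpret. The Sample Size section allows for 20% dropout, and Data Analysis calls on intention-to-treat when data are missing. If a patient scores sharply lower at T2 or does not attend, nothing in the article says that events in the preceding 11 weeks will have been asked about. An explanation may then be missing, or may reach the investigators for some patients and not others.

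**Working it through.** The protocol gives no figure on this point to reproduce, so the check compares the stated time windows.

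**Inputs**
- Treatment length: 2 weeks (Interventions: "each participant receives 10 sessions of cerebellar cTBS coupled with SLT (5 sessions per week) within 2 weeks").
- Adverse-effect window: treatment plus 1 week (Safety).
- Last outcome visit: 12 weeks after treatment, ±3 days (Study Design, Table 1).
- Patients: 40, 20 per arm (Sample Size).

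**Share of time outside the adverse-effect window**
- After treatment: (12 − 1)/12 = 11/12 = 91.7%.
- With the visit window, early T2: 84 − 3 = 81 days, and 81 − 7 = 74 days outside; 74/81 = 91.4%.
- With the visit window, late T2: 84 + 3 = 87 days, and 87 − 7 = 80 days outside; 80/87 = 92.0%.
- From the first session: (12 − 1)/(2 + 12) = 11/14 = 78.6%.

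**What is stated for those 11 weeks**

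| Item | Treatment to week 1 | Week 1 to week 12 |
|---|---|---|
| Non-serious adverse effects | Reported by the investigator | No stated route |
| Serious incidents | Reported; ethics committee notified | Ethics committee notified (no end date) |
| Inquiry about events at T2 | – | Not stated |
| Recording of events by arm | Not stated | Not stated |

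**Could any event be expected in the gap?** The documents give no event rate, so the rates below are assumptions. Let r be the chance that a patient has an event of any kind in the 12 weeks after treatment, at constant hazard, with all 40 patients followed. The chance of an event in the 11-week gap is p = 1 − (1 − r)^(11/12). The expected number is 40p, and the chance of at least one is 1 − (1 − p)^40.

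| Assumed r | p | Expected events (40p) | Chance of at least one |
|---|---|---|---|
| 1% | 0.0092 | 0.37 | 31% |
| 2% | 0.0183 | 0.73 | 52% |
| 5% | 0.0459 | 1.84 | 85% |
| 10% | 0.0921 | 3.68 | 98% |

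Across this range, at least one event in the gap is a realistic prospect, though the number would be small.

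**Seizures alone are not the issue.** At the stated 0.02%, the chance of at least one seizure among 20 real-cTBS patients is 1 − (1 − 0.0002)^20 = 0.4% if the risk is per patient. If it is per session (20 × 10 = 200 sessions), it is 1 − (1 − 0.0002)^200 = 3.9%.

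**The case against.** The strongest objection is the serious-incident sentence. It has no end date, and a recurrent stroke or late seizure would plainly count. A reader might infer from the 1-week rule that such events fall outside any rule, or that 79% of follow-up is unobserved. The documents do not support either reading: serious incidents keep a reporting route throughout, and patients are seen at T2. The 11/14 above is only the share of time outside the adverse-effect window. What remains is that the sentence governs notification of incidents that come to attention. It plans no inquiry at T2 and no recording by arm, and it does not reach non-serious events.

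Other objections:

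- **The short window has a reason.** Seizure timing is stated, and the Introduction puts the inhibitory effect of a stimulation at up to 60 minutes. That supports a short window for acute stimulation effects. It does not cover the broad definition, in a trial that looks for benefit at 12 weeks.
- **The article is condensed.** The full protocol may provide for questions at T2. That is possible, but the article states a window explicitly, and it is the stated window that is at issue. The lack of an adverse-effect row at T2 in Table 1 proves little by itself, because the table has no such row at any visit, including T1, which lies inside the window.
- **The sentence may be a reporting deadline.** The neighbouring sentence on MRI effects sets a 24-hour one. A collection window is the more natural reading. If a deadline was meant, the collection period is unstated and still needs clarifying.
- **Effect on the T2 means.** A reader might reason that one patient losing, say, 20 AQ points would move an arm mean by 20/20 = 1 point. The 20-point loss has no basis in the documents. Recording the event would not remove the shift either, since under intention-to-treat the score stays in. It would only help to explain it.

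**Conclusion.** The point holds in a limited form. The stated adverse-effect window ends 1 week after treatment, and outcomes continue to week 12, so 11 of 12 post-treatment weeks (91.4% to 92.0% across the visit window) lie outside it. In that time only serious incidents have a stated route, and that route is notification to the ethics committee. No inquiry at T2 and no by-arm recording of later events is stated.

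This rests on reading the 1-week sentence as a collection window and on the article alone. It does not depend on the assumed event rates, which serve only for scale. The documents do not show that serious events go unreported or that any treatment estimate is biased. It is a worthwhile low-cost improvement to safety reporting and to the interpretation of T2 scores, and not a flaw in the primary analysis.

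**What to change.** 1. At the existing T2 visit, ask patients in both arms, with the same questions, about any adverse event since the 1-week window closed. Name serious events, seizure, new stroke and worsening of language specifically. Where a patient misses T2, seek the same information when the reason for absence is recorded.
2. Report events by arm for T0–T1 and T1–T2. T1 falls within ±3 days of the end of treatment, so the 1-week window closes 7 − 3 = 4 to 7 + 3 = 10 days after T1. Events in that stretch belong to the T1–T2 period.
3. Reconcile the 1-week sentence with the open-ended serious-incident sentence in the Safety section, saying which events each covers and until when. If the 1 week is a reporting deadline, state the collection period separately.

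The cost is a few questions at a visit already scheduled, plus a short by-arm table. The downside is that some recorded events will be unrelated to stimulation; asking both arms in the same way lets the sham arm show that background.
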